#### Validation of the CAREPAL-8 Screening Tool

The data used to evaluate the psychometric properties of the CAREPAL-8 will be collected completely without planned missing values. To assess convergent validity, Pearson correlation analyses between index 1 and the scores of the GAD-7, PHQ-9, and both component scores of the SF-8, and between index 2 and the FIN will be conducted using baseline data. We expect high correlations of at least |*r*|=0.50. In our first version of the study protocol in 2022, we originally expected at least |*r*|=0.70. After further methodological considerations and before data analyses, we adjusted this value. According to the recommendations of Cohen [64], both values are interpreted as high. Sensitivity to change will be evaluated by using the patient’s care setting during the longitudinal observation as an external criterion, categorizing ICs in 2 groups: those who experienced at least 1 transition between outpatient and inpatient care (or vice versa) and those who did not transition. Clinically, it can be assumed that these transitions occur in response to significant changes in the patient’s health status or in the capacities of the ICs (eg, decompensation of home care due to IC overload) and are reflected in changes in the indices. We will evaluate whether a minimally important difference of 0.5 SD exists between these groups for each index. As an additional criterion, we will analyze the free-text item about recent events that have changed the burden and needs of the IC. The longitudinal data used in these analyses are part of the fixed block X, which is implemented in every questionnaire version. Supplementary analyses will assess the sensitivity and specificity of the instrument by determining cutoffs based on receiver operating characteristic analyses for both indices (index 1: PSYQOL and index 2: NEEDS). From this, we will analyze which cutoff for each index best predicts a change in care setting (transition vs no-transition group).

Statistical analyses will be conducted using the statistical software packages R (version 4.1.2 or newer; R Foundation for Statistical Computing) and SPSS Statistics (version 29 or newer; IBM Corp).

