### Instruments

#### Overview

To record ICs’ burden and needs, the baseline questionnaire and follow-up questionnaires consist of the following validated scales (German versions): DT of the National Comprehensive Cancer Network [41,42], Generalized Anxiety Disorder 7-item scale (GAD-7) [43,44], PHQ-9 [10,11,45], Short-Form Health Survey (SF-8) [46,47], Family Inventory of Needs (FIN) [48,49], and Oslo Social Support Scale (OSLO-3) [50,51]. While the FIN was specifically developed for assessing the needs of ICs of severely ill people, most of the questionnaires are generic (GAD-7, PHQ-9, and SF-8). The DT was originally developed for patients with cancer, but is also validated for the screening of ICs [9]. Previous studies have shown the feasibility of similar questionnaire surveys with ICs in SPC [34,52]. To align with the weekly assessment schedule, the recall periods of the GAD-7 and PHQ-9 were adapted from 2 weeks to 1 week. This adjustment was made to ensure consistency with the measurement intervals and to avoid overlap between consecutive assessments.

The instrument to be validated, the CAREPAL-8, is also part of each questionnaire. The CAREPAL-8 is a newly developed multidimensional 8-item screening instrument of IC burden in palliative care [12]. It was developed in a data-driven approach and consists of single items of the GAD-7, PHQ-9, SF-8, and FIN [12]. For the analysis, each item is dichotomized. By summarizing 4 items each, 2 indices are calculated: index 1 measuring psychopathological symptoms and quality of life (PSYQOL) and index 2 measuring the fulfillment of needs (NEEDS) [12]. By combining both indices, ICs are allocated to one of four groups with different risk profiles: (1) currently stable ICs (index 1=0 and index 2≤1), (2) ICs with unmet needs (index 1=0 and index 2≥2), (3) psychologically burdened ICs (index 1≥1 and index 2≤1), and (4) high-risk ICs (index 1≥1 and index 2≥2) [12]. For each group, the authors included clinical recommendations for further IC assessment and support [12]. Table 1 gives an overview of the included scales.

**Table 1. T1:** Included scales^a^.

Outcome	Questionnaire or scale	Description	Analyses

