Needs	Family Inventory of Needs (FIN)	Measures the needs of family caregivers of severely ill patients in terms of their current importance and fulfillment [48,49]. Contains 20 items that are each rated on 2 subscales: FIN-Importance, ranging from 1=not important to 5=extremely important, and FIN-Fulfillment, ranging from 0=not met, 0.5=partly met to 1=met [49].	The scale FIN-Importance is dichotomized into 0=not or somewhat or moderate vs 1=very or extremely important. The scale FIN-Fulfillment is dichotomized into 0=not or partly met and 1=met. In addition to the sum scores of the number of important and unfulfilled needs (scale 0‐20 in each case), corresponding values can also be calculated for 4 dimensions of the FIN: basic information (scale 0‐4), information on treatment and care (scale 0‐7), support (scale 0‐7), and patient comfort (scale 0‐2) [53]. The German version was used with the courtesy of Schur et al [49].
Social support	Oslo Social Support Scale (OSLO-3)	OSLO-3 is a 3-item instrument that measures the current extent of perceived social support on a 4- or 5-point Likert scale with respect to the number of close confidants, the concern from others, and the accessibility of practical help from neighbors [50].	Calculation and analysis of a sum score (ranging from 3 to 14). Suggested cutoffs are 3‐8=poor social support, 9‐11=moderate social support, and 12‐14=strong social support [54].
Multidimensional informal caregiver (IC) burden	8-Item Screening Tool for Family Caregiver Burden in Palliative Care (CAREPAL-8)	Newly developed multidimensional 8-item screening instrument of IC burden to be validated in this study [12]. Consists of single items from established scales that had been identified to be most predictive for allocation of ICs to 4 groups with distinct risk profiles. Includes items from GAD-7 (item 2), PHQ-9 (item 4), SF-8 (item 4 and item 8), and FIN (item 6, item 11, item 16, and item 17).	Two indices are calculated. Index 1 for psychopathological symptoms and quality of life (PSYQOL), consisting of the selected items of the GAD-7, PHQ-9, and SF-8. Index 2 for needs (NEEDS), consisting of the FIN items. The combination of both indices forms the basis for assigning ICs to 4 different risk profiles: currently stable ICs, ICs with unmet needs, psychologically burdened ICs, and high-risk ICs.

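### The CAREPAL-8 convergent validity correlations share items with their comparison scales, which inflates all of them and takes index 2 vs FIN close to the 0.50 benchmark by construction

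*Protocol article*

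**What the plan says.** The Overview under Instruments states that the CAREPAL-8 "consists of single items of the GAD-7, PHQ-9, SF-8, and FIN". The CAREPAL-8 row of Table 1 identifies the items. Index 1 (PSYQOL) uses GAD-7 item 2, PHQ-9 item 4 and SF-8 items 4 and 8. Index 2 (NEEDS) uses FIN items 6, 11, 16 and 17. Each item is dichotomized and each index adds up four items.

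Under Statistical Analyses, Validation of the CAREPAL-8 Screening Tool, convergent validity of the first index is assessed by "Pearson correlation analyses between index 1 and the scores of the GAD-7, PHQ-9, and both component scores of the SF-8". For the second index the sentence goes on to say that the same kind of analysis is planned: "and between index 2 and the FIN will be conducted using baseline data". The benchmark reads "We expect high correlations of at least |*r*|=0.50". The same paragraph discloses that in the 2022 protocol version "we originally expected at least |*r*|=0.70", and that the value was changed before data analysis. The section does not say that shared items are removed from the comparison scores, does not mention the overlap, and does not say which FIN score is meant. The sample size section plans 219 ICs for this analysis, from r = 0.50 and a 95% CI of total width 0.20.

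**The concern.** A convergent validity correlation should show that an instrument agrees with a separate measure of the same construct. Here the same answer, with the same measurement error, enters both sides. For index 2 this applies to all four items. Part of each correlation is therefore guaranteed by construction, and the 0.50 benchmark does not allow for it.

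This affects study aim 2. Convergent validity is the only validation analysis with its own sample size, and the Conclusions tie use of the tool in daily practice to its proving valid. If index 2 is supported mainly because it correlates with itself inside the FIN, readers learn little about whether four needs represent the remaining 16.

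**Working it through.** **Inputs from the protocol.** Four items per index. Scale lengths: GAD-7 7, PHQ-9 9, SF-8 8, FIN 20. Shared items: 1, 1, 2 and 4 respectively. Benchmark 0.50; N = 219.

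**Assumptions (not in the protocol).** Equal item variances, a common inter-item correlation rho, an unweighted SF-8 sum (the component weights are not given), and a 20-item FIN unmet-needs score coded as in index 2.

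**Step 1: the protocol's own figure.** Fisher z interval at n = 219: 1.96/√216 = 0.1334 and atanh(0.50) = 0.5493. The limits are tanh(0.4159) = 0.3935 and tanh(0.6827) = 0.5932, a width of 0.1997. At n = 218 the width is 0.2002. The figure of 219 is reproduced.

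**Step 2: formula.** For a k-item index and an m-item sum sharing s items,

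r = [s + (km − s)·rho] / √{[k + k(k−1)·rho]·[m + m(m−1)·rho]}.

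At rho = 0 this is s/√(km), the part due to overlap alone. The overlap-free version drops the shared items from the scale (m becomes m − s, s becomes 0).

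**Step 3: overlap alone (rho = 0).**
- Index 2 vs FIN: 4/√80 = 0.447
- Index 1 vs SF-8 sum: 2/√32 = 0.354
- Index 1 vs GAD-7: 1/√28 = 0.189
- Index 1 vs PHQ-9: 1/√36 = 0.167

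**Step 4: index 2 vs FIN.** Planned: (4 + 76rho)/√[(4 + 12rho)(20 + 380rho)]. Overlap-free: 64rho/√[(4 + 12rho)(16 + 240rho)].

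| rho | planned r | r with the other 16 items |
|---|---|---|
| 0 | 0.447 | 0 |
| 0.0164 | 0.500 | 0.11 |
| 0.05 | 0.582 | 0.282 |
| 0.10 | 0.668 | 0.444 |
| 0.124 | above 0.50 | 0.50 |
| 0.15 | 0.729 | 0.553 |
| 0.20 | 0.775 | 0.632 |

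Between rho of about 0.016 and 0.124 the planned correlation passes and the overlap-free one does not.

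*Unequal variances.* With fully independent items, r = √[V4/(V4 + V16)], where V4 and V16 are the summed variances of the index items and the other items. This reaches 0.50 when V4/V16 = 1/3, so each index item needs 16/(4 × 3) = 1.33 times the variance of each other item. For example, prevalences of 0.5 and 0.2 give V4 = 4 × 0.25 = 1 and V16 = 16 × 0.16 = 2.56, hence r = √(1/3.56) = 0.53.

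**Step 5: index 1, shared items dropped from the scale (planned → overlap-free).**

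| rho | GAD-7 | PHQ-9 | SF-8 sum |
|---|---|---|---|
| 0.10 | 0.485 → 0.351 | 0.490 → 0.381 | 0.595 → 0.351 |
| 0.15 | 0.575 → 0.461 | 0.583 → 0.492 | 0.666 → 0.461 |
| 0.20 | 0.645 → 0.548 | 0.654 → 0.577 | 0.722 → 0.548 |

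The rho needed for 0.50 moves from 0.108 to 0.171 (GAD-7), 0.105 to 0.154 (PHQ-9) and 0.051 to 0.171 (SF-8 sum). Dichotomizing the index items lowers the overlap part somewhat.

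**Step 6: the SF-8 alternative.** If the two SF-8 items are instead dropped from index 1, k = 2, m = 8 and s = 0, so r = 16rho/√[(2 + 2rho)(8 + 56rho)]. At rho = 0.15 this is 2.4/√(2.3 × 16.4) = 0.39; at rho = 0.22 it is 3.52/√(2.44 × 20.32) = 0.50. The reduced index is shorter and correlates less for that reason too.

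**The case against.** The strongest reply is that the range where overlap decides the FIN result may be unrealistic. In the same model Cronbach's alpha is 20rho/(1 + 19rho): about 0.25 at rho = 0.016 and 0.74 at rho = 0.124. The protocol describes the FIN as a validated scale; if its items cohere better than that, both versions pass. This stands as a limit on the size. It is not a reason to keep the shared items, because the protocol gives no inter-item correlation and the four FIN dimensions could lower the average.

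For index 1 the verdict also depends on the inputs. In simulations with dichotomized index items and latent item correlations of 0.4 within and 0.2 between scales, GAD-7 falls from 0.51 to 0.45 and PHQ-9 from 0.51 to 0.47. At 0.4 and 0.3 they fall only from 0.61 to 0.55 and from 0.62 to 0.57. The verdict changes only near the benchmark.

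Three stronger readings are tempting and not supported:

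- A reader might infer that overlap alone satisfies the benchmark throughout. It does not for index 1. For index 2 it gives 0.447 under equal variances and passes only with a small positive rho, unequal variances or sampling error.
- A reader might infer that the CAREPAL-8 could be declared valid on overlap. The protocol words 0.50 as an expectation, not a pass/fail rule, and also plans sensitivity to change using care-setting transitions and a free-text events item, neither of which is a CAREPAL-8 item.
- A reader might see the move from 0.70 to 0.50 as a way to exploit the overlap. It is disclosed and stated to precede data analysis; it adds no separate defect.

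**Conclusion.** The point holds in limited form. Every planned convergent correlation is part-whole, no correction is stated, and all are inflated. The inflation is serious for index 2 vs FIN, where the overlap contribution of 0.447 lies just below the benchmark, so a value slightly above 0.50 would say almost nothing about the other 16 needs. For index 1 the inflation is moderate and matters only when the overlap-free value lies near 0.50.

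The figures rest on equal variances and a common rho, neither given in the protocol. The FIN figures further assume the unmet-needs score; with the FIN-Importance score the overlap would be less direct. The SF-8 figure is only indicative. Severity: should be fixed before the validation is reported. The design, the data and the sample size of 219 are unaffected.

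**What to change.** 1. Name the FIN score used against index 2.
2. Apply the 0.50 benchmark to correlations with shared items removed: index 1 vs GAD-7 without item 2, index 1 vs PHQ-9 without item 4, and index 2 vs FIN without items 6, 11, 16 and 17.
3. For the SF-8 component scores, report an overlap-free version (index 1 without its two SF-8 items) alongside the planned one, noting that it tests a reduced index and not the one that assigns risk groups.
4. Report the uncorrected values as secondary, labelled as containing shared items.
5. Optionally, add the Distress Thermometer as an overlap-free comparator for index 1 only; it measures distress and is not an obvious criterion for needs.

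The cost is analysis wording and a few lines of code, since all items are collected at baseline without planned missingness. The downside is that the correlations will be smaller and some may miss 0.50. Dropping the shared items also removes some genuine common variance, so the choice to keep 0.50 for the corrected values should be stated before the data are analysed.

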Questionnaires are available exclusively in paper-pencil format and are either handed to the ICs in person, left at the patient’s care location, or sent by mail. In exceptional circumstances (eg, if a willing IC is on vacation abroad), the questionnaire may be completed via a structured telephone interview conducted by study staff, with this process duly documented. If necessary, the ICs may receive assistance from study staff or another person in completing the questionnaire; any such support is recorded in the respective questionnaire. These factors may be accounted for in the analyses as potential covariates. All pseudonymized questionnaires are returned by the ICs via prepaid envelopes or by study staff via mail, fax, or scan to the leading center for data entry and evaluation. Secured cloud systems with pseudonymized shared charts to document the distribution and receipt of questionnaires are used to coordinate data collection between study centers. Participation in the study will end either after 11 weeks of longitudinal data collection, upon the patient’s death, or if the IC withdraws from the study. Figure 1 illustrates the recruitment and data collection procedure.

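### The sensitivity-to-change comparison pools both transition directions and leaves follow-up unequal, which can dilute a real response or add a spurious one to the 0.5 SD result

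*Protocol article*

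**What the plan says.** The section Validation of the CAREPAL-8 Screening Tool takes the patient's "care setting during the longitudinal observation as an external criterion, categorizing ICs in 2 groups". The groups are "those who experienced at least 1 transition between outpatient and inpatient care (or vice versa) and those who did not transition". The reason given is that "these transitions occur in response to significant changes in the patient’s health status or in the capacities of the ICs"; the one example offered is a breakdown of home care through caregiver overload. The success criterion is: "We will evaluate whether a minimally important difference of 0.5 SD exists between these groups for each index". The same two groups are the outcome when ROC cutoffs are chosen. A second criterion is named: "As an additional criterion, we will analyze the free-text item about recent events that have changed the burden and needs of the IC".

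Follow-up length varies. The Data Collection section states: "Participation in the study will end either after 11 weeks of longitudinal data collection, upon the patient’s death, or if the IC withdraws". Ethical Considerations expects many patients to die within weeks of admission, and the Discussion anticipates high attrition. A Weibull joint model for death is described only for the trajectory aim. Under Study Design and Setting, ICs are recruited from 11 palliative care wards, 5 hospital teams and 8 home care teams, so a first transition can go either way.

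**The concern.** Two features of the stated grouping affect what the 0.5 SD comparison can show.

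- **Direction.** A move into inpatient care and a move home count as the same event. The stated rationale is about deterioration, but the pooled group also contains discharges. If the two kinds of move shift burden differently, a signed average understates the response to either.
- **Opportunity.** Whether an IC has at least one transition depends on how long the IC is observed. An IC whose patient dies in week 2 has had little chance to transition and will usually count as no transition. Follow-up length is then a confounder of the group comparison, and nothing stated for this analysis deals with it.

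The first feature can make a responsive index miss 0.5 SD. The second can push an unresponsive index towards it. The ROC analysis inherits the second problem, because early leavers count as non-events.

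**Working it through.** **The plan's own figures.** The article gives no sample size for sensitivity to change. Its other two figures reproduce:
- One-way ANOVA with 6 groups of 85, η²=0.025, f²=0.025/0.975=0.0256 and two-sided 5% gives power 0.804.
- A Fisher z interval at r=0.50 and n=219 has width 0.1997, against a target of 0.20.

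Neither depends on what follows.

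**Step 1: pooling of directions.** Let p be the share of transitions into inpatient care, d₁ their mean effect on the index and d₂ the mean effect of the reverse move, both in SD units relative to no transition. The pooled signed difference is p·d₁ + (1−p)·d₂. All values of p, d₁ and d₂ are assumed.

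| d₁ | d₂ | p | Pooled difference (SD) |
|---|---|---|---|
| 0.5 | 0.5 | any | 0.50 (no loss) |
| 0.5 | 0 | 0.5 | 0.25 |
| 0.5 | −0.5 | 0.5 | 0 |
| 0.5 | −0.5 | 0.7 | 0.35 − 0.15 = 0.20 |
| 0.5 | −0.5 | 0.9 | 0.45 − 0.05 = 0.40 |
| 0.8 | −0.5 | 0.7 | 0.56 − 0.15 = 0.41 |

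**Step 2: opportunity to transition.** With weekly transition probability h, the chance of at least one transition over n follow-ups is 1 − (1−h)ⁿ. At an assumed h=0.05 this is 5% for n=1 and 1 − 0.95¹⁰ = 40% for n=10.

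**Step 3: resulting gap in follow-up.** Assumptions: exponential survival with median 3, 5 or 8 weeks; h of 0.05, 0.10 or 0.20; at least one follow-up and at most ten; transitions unrelated to the index. Weekly survival is s = 2^(−1/median). The number of follow-ups n has probability s^(n−1)(1−s) for n=1 to 9 and s⁹ for n=10. Weighting by (1−h)ⁿ gives the no-transition group, and by 1 − (1−h)ⁿ the transition group. Across the nine combinations, mean follow-up is 5.7-8.5 weeks with a transition and 2.8-6.4 weeks without. For example:
- median 8, h=0.05: 8.45 against 6.38 weeks, a gap of about 2.06 (the smallest);
- median 5, h=0.10: 7.41 against 4.62, a gap of 2.79;
- median 8, h=0.20: 8.02 against 4.35, a gap of 3.67 (the largest).

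**Step 4: spurious difference when transitions have no effect.** For last-minus-baseline change this is the weekly drift times the gap.

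| Drift (SD/week) | Arithmetic | Range (SD) |
|---|---|---|
| 0 | 0 × gap | about 0 |
| 0.05 | 0.05 × 2.06 to 0.05 × 3.67 | 0.10-0.18 |
| 0.10 | 0.10 × 2.06 to 0.10 × 3.67 | 0.21-0.37 |
| 0.15 | 0.15 × 2.06 to 0.15 × 3.67 | 0.31-0.55 |

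A simulation of the same set-up agrees within sampling error (0.10-0.19, 0.20-0.37 and 0.31-0.55). If the score is instead the largest change from baseline, the simulation gives 0.17-0.35 SD even with no drift, because longer follow-up offers more chances of an extreme value (assumed within-person correlation 0.6).

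**Step 5: effect of the remedy.** In the same simulation, over 36 scenarios (3 medians × 3 values of h × 4 drifts) with no true effect, comparing at equal follow-up brought the difference within 0.015 SD of zero. Aligning change to the transition week brought it within 0.012 SD.

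**The case against.** Much of the opposing case is sound and limits the point.

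- **Cancellation is conditional.** It needs a signed score and effects that differ by direction. The article defines no change score and does not say that going home lowers burden. An absolute change would not cancel, although it would give up the expected sign and leave the follow-up problem. This stands.
- **Drift is not established.** The Introduction cites studies with rising burden and others with a flat course. Without drift, the artefact in last-minus-baseline change is about 0. This stands.
- **A reader might infer that an unresponsive index would pass on bias alone.** At drifts of 0.05-0.10 SD per week, the last-minus-baseline artefact stays below 0.5 SD. It reaches 0.5 SD only at the top of the assumed ranges.
- **A reader might infer that the comparison is simply long against short follow-up.** It is not: the groups are defined by a specific care-setting transition, and follow-up length is a confounder.
- **A reader might count it as an error that the index change is not tied to questionnaires around the transition.** Which questionnaires enter the score is a detail that an article may leave to the full protocol.
- **Very short follow-up is partly removed.** Imminent death is an exclusion criterion, and the target sample has at least one follow-up. The calculation above already requires one follow-up, and the gap remains.

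These limits do not change the grouping. Pooled directions, the open observation window and the 0.5 SD threshold are all fixed in the article.

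**Conclusion.** The concern holds in a conditional form. As written, the 0.5 SD comparison is hard to interpret in either direction. A true one-direction effect of 0.5 SD can shrink to 0.25 SD or to 0 at a 50:50 mix, given a signed score and differing effects. Unequal follow-up can add roughly 0.1-0.4 SD to last-minus-baseline change at drifts of 0.05-0.10 SD per week, and nothing material without drift. If the largest change is used, a difference arises even without drift. Survival, transition rates, direction mix, effects and drift are all assumed, because the article reports none.

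A reader might go further and conclude that sensitivity to change cannot be assessed at all. The document does not support that: the free-text criterion does not depend on this grouping, and the weekly data allow a better comparison. This should be fixed before the analysis, but it concerns one component of the second aim and leaves N=510 and n=219 untouched.

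**What to change.** - Report outpatient-to-inpatient and inpatient-to-outpatient transitions separately, each with its expected sign for each index stated before analysis.
- Compare each with ICs still under observation and not yet transitioned at the same follow-up week, or otherwise match or adjust for follow-up length. Apply the 0.5 SD criterion to that difference.
- Use the same time-matched groups for the ROC analysis.
- Define the change window around the transition so that it includes earlier weeks, for example change from an earlier questionnaire as well as from the last one before the move. The article itself says transitions respond to change, so burden may rise beforehand, and a single last-before to first-after window could miss that rise.

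**Cost.** Analysis wording and programming only: care situation, completion date and the CAREPAL-8 are in the fixed block of every follow-up questionnaire. The price is two smaller transition groups and wider intervals.

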#### Longitudinal Assessment of Burdens and Needs

As the number of trajectory types is an outcome of this exploratory study, sample size calculation for GMMs is not feasible due to the uncertainty of key parameters. As a proxy, a mean comparison of the baseline variables between trajectory types is used. An IC is part of the analysis population if the baseline data and at least 1 follow-up questionnaire are valid. Various scenarios with 3 to 6 trajectory types were calculated.

Assuming, for reasons of clinical practicability, a highest number of 6 trajectory types and a small effect size (η^2^=0.025), we would need 85 ICs per group (total of 510 ICs) to detect this effect size with a power of 80% and a 2-sided type I error of 5%. This calculation assumes equal group sizes.

Sijbrandij et al [65] examined cases where estimation or performance issues arise when using GMMs. The authors concluded that no performance issues occur with sample sizes of 1000 individuals, while sample sizes of 300 individuals can present performance challenges, which can only be addressed by limiting variance parameters. Furthermore, we cite the study of Kim [66], which investigates GMMs in the sample size range targeted in this study. Additionally, we searched for studies using GMMs [67-72], which included sample sizes ranging from 129 to 6987 individuals. Our targeted sample size of 510 ICs is on the lower end of this range, but it is similar to another study conducted in the palliative care setting [71].

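### Sensitivity and specificity of the CAREPAL-8 indices are to be read at ROC cutoffs chosen in the same caregivers; under Youden-type selection this overstates accuracy by a few points

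*Protocol article*

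**What the plan says.** The relevant text is in the Protocol article, Statistical Analyses, under Validation of the CAREPAL-8 Screening Tool. After convergent validity and sensitivity to change, it adds: "Supplementary analyses will assess the sensitivity and specificity of the instrument by determining cutoffs based on receiver operating characteristic analyses for both indices". The aim is then stated: "we will analyze which cutoff for each index best predicts a change in care setting (transition vs no-transition group". The two groups being separated are "those who experienced at least 1 transition between outpatient and inpatient care (or vice versa) and those who did not transition".

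Under Instruments, Overview, the items are dichotomized and "By summarizing 4 items each, 2 indices are calculated", so each index runs from 0 to 4. The same paragraph already gives the tool its thresholds, for example "high-risk ICs (index 1≥1 and index 2≥2". The validation section does not say that accuracy will be reported at these thresholds.

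**The concern.** The section finds the best cutoff and assesses accuracy in one step, in one cohort. The best of several estimated cutoffs is partly best by chance, and that chance element is counted as accuracy when performance is read from the same data. If followed as written with a Youden-type criterion, the published sensitivity and specificity would be somewhat too favourable for a tool meant for routine screening.

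The aim also matters here. Aim 2 is to validate an existing tool whose thresholds define its four risk groups. Accuracy at a newly derived cutoff need not describe that tool.

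**Working it through.** **Figures the plan gives.** None is given for the ROC analysis. The two sample sizes reproduce and supply the N used below.
- Aim 1: "we would need 85 ICs per group (total of 510 ICs) to detect this effect size with a power of 80", with "a highest number of 6 trajectory types and a small effect size (η^2^=0.025". f² = 0.025/0.975 = 0.02564, and the noncentrality is 510 × 0.02564 = 13.08 on 5 and 504 df. Power is 0.804 with 85 per group and 0.798 with 84.
- Convergent validity: atanh(0.50) = 0.549, half-width on that scale 1.96/√216 = 0.133. The back-transformed interval has width 0.1997 at n=219 and 0.2002 at n=218.

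**Definitions.** For cutoff c = 1, 2, 3, 4:
- Se(c) = P(index ≥ c | transition)
- Sp(c) = P(index < c | no transition)
- J(c) = Se(c) + Sp(c) − 1

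Let c* be the cutoff with the largest estimated J. The estimate at c* is at least as large as the estimate at any other cutoff. Its expectation is therefore at least the largest true J, which is at least the true J at c*. The bias under Youden selection cannot be negative. Under another criterion the maximised quantity is the one overstated, and that need not be Se + Sp.

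**Assumptions, because the article gives no values.** The index is the sum of four dichotomous items with latent correlation 0.5. The number of transitions and the true separation are varied.

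**Result 1, Youden selection.** N=510, item prevalence 30% to 50%, 4000 replicates per cell. Overstatement of Se + Sp in percentage points:

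| Transition rate | AUC 0.50 | AUC about 0.59 | AUC about 0.65 | AUC about 0.74 |
|---|---|---|---|---|
| 10% | 4.8 | 4.3 | 3.5 | 2.7 |
| 20% | 3.6 | 2.9 | 2.1 | 1.5 |
| 30% | 3.1 | 2.4 | 1.8 | 1.2 |
| 50% | 2.8 | 2.0 | 1.5 | 0.9 |

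At a cutoff fixed in advance the bias is within 0.2 points in every cell. At AUC about 0.59, the split is 3.8 points on sensitivity and 0.4 on specificity with 10% transitions, and 1.0 and 1.0 with 50%. If only 219 caregivers were analysed, the overstatement would be 2.2 to 7.0 points.

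**Result 2, 40 to 250 transitions among 510.** The overstatement under Youden is about 1.4 to 5.4 points. The top belongs to 40 transitions with no separation, the bottom to 250 transitions with clear separation.

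**Result 3, other criteria.** With item prevalence 40%, 100 transitions among 510 and a group difference of about 0.38 SD, the bias in Se + Sp is:
- Youden: +2.8 points
- Closest to the ROC corner: +1.1 points
- Maximum overall accuracy: −0.1 points, that is, about zero

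Across 40 to 250 transitions, closest-to-corner gives about 0.1 to 2.4 points. Maximum accuracy is near zero only while transitions are few. Overall accuracy is [m·Se + (N − m)·Sp]/N for m transitions, so it becomes equivalent to Youden as m approaches N/2.

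**AUC.** The index is a fixed sum with no fitted weights, and the AUC does not depend on the chosen cutoff. Its simulated bias was below 0.001.

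**The case against.** The strongest reply has four parts.

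1. The analysis is supplementary. Validation rests on correlations of at least 0.50 and on the 0.5 SD group comparison, and no sample size or decision rule uses the ROC cutoff. This stands and keeps the point minor.

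2. A journal article may leave internal validation to an analysis plan that is not shown. A reader might infer that the final report will give uncorrected values; the article does not establish that. What it does state is the procedure, and that procedure is biased under Youden-type selection unless a correction is added.

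3. A reader might infer that accuracy is inflated whatever the selection criterion. The article names no criterion, and Result 3 shows that the inflation can be small or absent. This part of the objection stands in full.

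4. The bias is smaller than the noise. At a fixed cutoff the standard error of J is about 4 to 5 points with 100 to 150 transitions and about 7 with 40. This is true, but the bias always has the same sign under Youden, so an ordinary interval at the selected cutoff is centred too high.

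Two further inferences are tempting. One is that the 0.5 SD target (an AUC of about Φ(0.5/√2) = 0.64 under normality) makes weak separation the expected result. The plan treats 0.5 SD as a minimally important difference to be examined, not as a forecast. The other is that a worthless index would look accurate. With no true relation the apparent J is only about 0.03 to 0.06, which few readers would take for useful accuracy.

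**Conclusion.** The point holds in a limited form. Choosing the cutoff and reading sensitivity and specificity in the same caregivers overstates their sum by about 1.4 to 5.4 points at N=510 with 40 to 250 transitions, if selection is by the Youden index or a similar rule. Very clear separation (AUC about 0.74) with balanced groups brings it to about 0.9. Few transitions and weak separation make it largest, and with a transition minority most of it falls on sensitivity.

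These sizes rest on assumed transition numbers, item prevalences and item correlation, and on the 0 to 4 index being the score analysed. Change scores would offer more cutoffs and a larger bias. The AUC, the convergent-validity correlations and the 0.5 SD comparison are not affected, and nothing here undermines the validation aim as a whole.

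**What to change.** 1. Report sensitivity and specificity with confidence intervals at the thresholds given under Instruments, Overview (index 1≥1, index 2≥2). They were set before this cohort, so they carry no selection bias in it, and they describe the tool that is being validated.
2. Label any ROC-derived cutoff exploratory and name its selection criterion in advance.
3. For that cutoff, give bootstrap optimism-corrected sensitivity and specificity. Resample caregivers, re-select the cutoff in each resample, take its apparent accuracy there minus its accuracy in the full sample, and subtract the mean difference. This removes most of the bias, not all of it, and the report should say so.
4. Report the AUC without optimism correction.

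The cost is a short bootstrap in R, which is already planned software. No new data are needed and no other analysis changes. The accuracy figures become slightly less favourable.
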